### Sample size

A power analysis was conducted using G*Power software (version 3.1.9.4) for a one-way ANOVA (fixed effects, omnibus) with three groups. Assuming a medium effect size (f = 0.25), α = 0.05, and a desired power of 0.80, the analysis yielded a required sample size of 159 participants, with a critical F-value of 3.054. To accommodate an expected dropout rate of 10%, the sample size was adjusted using the proportional method, resulting in a final target of 177 participants (59 per group). This adjustment ensures that statistical power remains adequate even if participant attrition occurs. Study 2 will include 45 participants (n = 15 per group) as part of a proof-of-concept trial intended for preliminary exploration. For Study 1, biological samples (fecal) will be collected from a randomly selected subgroup of 90 participants (30 per group) before and after the interventions. Furthermore, a subset of 24 participants (12 from each study) will be selected for the qualitative study using purposive sampling to capture diverse perspectives [67]. The sample size is based on previous studies [56,61,68] and evidence suggesting that qualitative inquiry often reaches data saturation with approximately 12 participants [69].

### Interventions

#### Online physical exercise and mind-body interventions.

The training program will run for 12 weeks, consisting of three sessions per week, all conducted remotely. Participants will take part in weekly synchronous sessions in groups of 15 and will also complete autonomous sessions on days of their choice. Sessions will be conducted using a secure version of Zoom with end-to-end encryption and privacy settings, following recommended standards for technology-based health interventions [70]. An orientation session will be held at the beginning to introduce the program, weekly schedules, required materials, safety guidelines, proper exercise techniques, training on the Zoom platform, and a question-and-answer segment. To participate in the training sessions, participants will need the following materials: (1) a digital device (computer, tablet, or mobile phone) with an internet connection, camera, and microphone; (2) basic training items, including an exercise mat, armchair or sofa, towel, full water bottle, and comfortable workout attire, depending on the specific interventions; and (3) additional materials, which will be outlined in the following sections. With participants’ prior consent, Zoom sessions led by instructors will be recorded to facilitate participant review and repetition, and also to support training quality assurance and research purposes. These recordings will be securely stored on university-hosted cloud storage. Each group will be encouraged to use a dedicated WhatsApp group to connect with one another and the research team, fostering an environment conducive to sharing experiences.

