### Statistical analyses

Data will be entered into a version-controlled Excel database. Analyses will be conducted using the latest available versions of IBM SPSS Statistics and R. A two-tailed p-value < 0.05 will denote statistical significance, with adjustments for multiple comparisons applied where appropriate. Descriptive statistics (means, standard deviations, medians, ranges, and frequencies) will summarize baseline characteristics overall and by group. We will assess distributional assumptions, including skewness and the presence of outliers. Missing data will be characterized by reporting the percentage of missing values for each variable and by evaluating the most likely mechanisms, classified as missing completely at random (MCAR), missing at random (MAR), or missing not at random (MNAR).

Primary hypotheses will be tested under an intention-to-treat (ITT) framework, including all randomized participants. Analysis of covariance (ANCOVA) will model change scores (post-intervention – baseline) using group, baseline score, and selected covariates as predictors. Sex and age will be included as covariates in all analyses. Additional covariates will be considered from a pool of theoretically relevant candidates if they show a significant and meaningful association with the outcomes. To minimize multicollinearity, we will examine the interrelationships among selected predictors and retain only one variable when substantial overlap is observed. If the omnibus test is significant, we will perform pairwise comparisons within each outcome variable using appropriate corrections for multiple comparisons (e.g., Bonferroni). Assumptions of homogeneity of regression slopes, normality, and homoscedasticity of residuals will be checked. If violated, alternative models (e.g., mixed-effects models for repeated measures) will be considered. Between-group findings will be supplemented by within-group analyses (paired t-tests or Wilcoxon tests, as appropriate).

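### Study 1 teaches every arm in live classes of about 15, but its sample size and primary ANCOVA assume independent participants; any positive class-level ICC makes the arm contrasts anti-conservative and the 0.80 power conditional

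*Protocol article*

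**What the plan says.** In the protocol article, the Randomization section allocates individuals 1:1:1 within each recruitment wave of Study 1. The section on the online interventions then sets the delivery format: "Participants will take part in weekly synchronous sessions in groups of 15". It adds: "Each group will be encouraged to use a dedicated WhatsApp group to connect with one another and the research team". The HIFT, MBSR and Qigong sections each describe weekly live sessions over a 12-week programme.

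The Sample size section uses a power calculation "for a one-way ANOVA (fixed effects, omnibus) with three groups". Its inputs are given as "Assuming a medium effect size (f = 0.25), α = 0.05, and a desired power of 0.80", and it "yielded a required sample size of 159 participants, with a critical F-value of 3.054". The only inflation is for attrition: "To accommodate an expected dropout rate of 10%, the sample size was adjusted using the proportional method", which gives 177, or 59 per arm. No ICC or design effect appears.

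The Statistical analyses section fixes the primary model as an ANCOVA of the change score "using group, baseline score, and selected covariates as predictors", with sex and age always included. The assumption checks cover parallel slopes, normal residuals and equal variance, but not independence. The one mixed model named is a fallback for repeated measurements, which deals with correlation within a person and not within a class.

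**The concern.** This is an individually randomised trial with group-delivered treatment. Before treatment the participants are independent. Afterwards, those taught in the same live class, who may also share a chat group, can drift together through peer interaction and through conditions specific to that class or to one arm in one wave. That shared component does not average out over individuals; it averages out only over the few classes in an arm. A model without it understates the variance of each arm mean.

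The contrasts between arms are the core of Study 1, because each programme is hypothesised to have its own profile of benefit. The omnibus test also opens the pairwise comparisons, so an anti-conservative omnibus test carries through to the headline claims. The primary outcomes include self-reported depression, anxiety and stress, on which classmates could plausibly influence each other.

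**Working it through.** **Inputs from the protocol article.** Three arms, f = 0.25, α = 0.05, N = 159 evaluable (53 per arm), 10% dropout, target 177 (59 per arm), classes of 15, three waves.

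**Assumed inputs.** ICC of 0.01, 0.02, 0.05 and 0.10, taken wholly at class level within arm. Classes per arm are inferred: 59/15 = 3.9, so about four; or six, if the roughly 20 per arm in each wave (59/3) are split in two. Analysed class size m is 159/12 = 13.25 or 159/18 = 8.83.

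**Step 1: the plan's own figure.** With λ = N·f² = 159 × 0.0625 = 9.94 and df (2, 156), the critical F is 3.054 and power is 0.805. Dropout: 159/0.9 = 176.7, so 177. The arithmetic is right under independence. There is little slack: at m = 13.25 an ICC of 0.001 already gives 0.7997.

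**Step 2: type I error of the planned test.** The between-arm mean square is inflated by DE = 1 + (m − 1)·ICC, and the within-arm mean square has expectation W = 1 − ICC·(m − 1)/52. With R = DE/W and the closed form for 2 numerator df, P(F > x) = (1 + 2x/156)^(−78), the error is this expression at x = 3.054/R. Example, four classes, ICC 0.05: DE = 1 + 12.25 × 0.05 = 1.6125; W = 0.988; R = 1.632; x = 1.872; error 0.157. Simulation of the unadjusted F test with 53 analysed per arm agrees (0.157 over 100,000 trials).

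| ICC | 4 classes per arm | 6 classes per arm |
|---|---|---|
| 0.01 | about 7% | about 6% |
| 0.02 | about 9% | about 7.5% |
| 0.05 | about 16% | about 12% |
| 0.10 | about 26% | about 19% |

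**Step 3: power of a test of correct size at f = 0.25, no credit for baseline.** Effective N = 159/DE and λ = 0.0625 × effective N. The first power figure keeps df (2, 156). The second uses class-level df, (2, 9) for four classes per arm and (2, 15) for six.

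| ICC | Classes per arm | DE | Effective N | Power, design effect only | Power, class-level df |
|---|---|---|---|---|---|
| 0.02 | 4 | 1.245 | 128 | 0.71 | 0.56 |
| 0.02 | 6 | 1.157 | 137 | 0.74 | 0.66 |
| 0.05 | 4 | 1.613 | 99 | 0.59 | 0.45 |
| 0.05 | 6 | 1.392 | 114 | 0.66 | 0.57 |

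**Step 4: possible gain from the baseline covariate.** If f = 0.25 is on the unadjusted scale and the baseline–outcome correlation is ρ, λ is divided by 1 − ρ² (ICC taken on the adjusted scale). With four classes per arm and ρ = 0.5, design-effect power is 0.83 at ICC 0.02 and 0.72 at ICC 0.05; with df (2, 9) it is 0.69 and 0.57. With ρ = 0.7 and df (2, 9) it is 0.85 and 0.75.

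**Step 5: which sources of correlation count.** With three waves, six classes of 9 per arm and ICC 0.05, the planned F test rejects about 4.6% under the null if all the correlation comes from wave, about 8% if it is half wave and half class, and about 12% if it is all class.

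**The case against.** The strongest objections concern mechanism and size.

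- **Wave and instructor.** A reader might infer that sharing a wave or a teacher inflates the error. The protocol does not support that. Wave is crossed with arm by the randomisation and cancels from the contrasts (Step 5). As described, HIFT and MBSR each have one instructor and Qigong has two who teach together, so staff appear constant within an arm. Instructor is confounded with arm, which limits interpretation and which a class term cannot cure. What remains is peer interaction and class-specific or arm-by-wave conditions. This objection stands.
- **No ICC is given.** Content is largely standardised, and at least one of the three weekly sessions is individual (two of three for MBSR), which may keep the ICC low. It would be too strong to say that false positives are far above 5%: at ICC 0.01–0.02 the error is 6–9%, and only from 0.05 upward is it large. This stands as a limit on size, not on direction.
- **Structure is inferred.** The number of classes and fixed class membership are not stated. The Discussion mentions flexible scheduling, and in the chat-group sentence the word group could mean the arm. Both layouts examined point the same way.
- **Power.** A reader might infer that the trial cannot reach 0.80. That is not established. Baseline adjustment may restore it (Step 4). Nor do the two consequences fall on the same test: the planned test still rejects about 0.78–0.80 of the time at f = 0.25, but at an inflated α; it is a test of correct size that loses power.
- **An unseen analysis plan might add a class term.** It might. But the basis of the sample size and the primary model are both stated in this article, and neither has one.

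**Conclusion.** The concern holds in conditional form. As written, the sample size and primary ANCOVA ignore the class structure that the protocol itself creates, and the arm-contrast standard errors are too small for any positive class-level ICC. At ICC zero there is no inflation. Over the assumed range of 0.01 to 0.10, the type I error of the nominal 5% omnibus test runs from about 6% to 26%.

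The stated 0.80 power is correct only under independence. How far a valid test falls short depends on the ICC, the class layout, the degrees of freedom and the baseline–outcome correlation. The protocol claims no credit for the last of these, and taking that credit would help power without correcting the error rate. Confidence is high in the direction and limited in the size.

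**What to change.** - **Analysis.** Account for synchronous class in the primary analysis of arm contrasts, by either a class random intercept with Kenward–Roger degrees of freedom or a cluster-robust variance with a small-sample correction. With about 12 to 18 classes in all, the small-sample correction is essential under either approach. Carry class into the multiple imputation.
- **Data.** Record each participant's class explicitly. Instructors already log attendance, so membership is probably recoverable, but the protocol does not say that the log identifies the class.
- **Reporting.** Report the estimated ICC. State that instructor effects cannot be separated from arm, so conclusions concern the programmes as delivered here.
- **Sample size section.** Keep the target and restate power as a range over assumed ICC and baseline correlation, using the expected analysed class size.

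The cost is a change of analysis wording, one recorded variable and a restated power figure. The downside is wider intervals and fewer error degrees of freedom. Data collection is planned to run to June 2026, so the change can be made before the analysis.

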#### High-intensity functional training intervention.

HIFT will consist of two 60-minute online group synchronous sessions, which will be recorded, and one individual autonomous session each week, during which participants can repeat a session of their choice from that week. Participants will need dumbbells or alternative items (e.g., water bottles, soda cans, or milk cartons) as weights for certain strength exercises, as well as a chair for support during specific movements. They will also receive a document explaining the Borg Scale (range: 6–20), with detailed descriptions of each score to assist them in monitoring effort during training [71]. The sessions will be organized as follows:

(1) Introduction (5 minutes): Welcome to the session and an overview of the training schedule, (2) Warm-up (10 minutes): Preparation for the exercise session through joint mobility exercises, dynamic stretching, and whole-body activities to elevate the heart rate, (3) Technique (10–20 minutes): Explanation and practice of proper exercise form for the movements included in the main session, with special attention to new exercises. This will be followed by an explanation of the specific type of HIFT to be performed that day, (4) Workout (15–25 minutes): The main portion of the session, consisting of HIFT drills, and (5) Cool-down (10 minutes): A gradual return to normal physiological levels through stretching exercises [12]. For the HIFT block, three distinct workout models commonly used in CrossFit training will be utilized and combined throughout the weeks: (1) Every Minute on the Minute (EMOM): Participants complete the prescribed number of repetitions for each exercise within one minute and use the remaining time for recovery, (2) As Many Rounds as Possible (AMRAP): Participants perform as many rounds as possible of the prescribed exercises and repetitions within a set time limit, and (3) For Time (FT): Participants complete the prescribed exercises and repetitions in the shortest time possible, within a predetermined time cap [72]. Table 1 presents the HIFT protocol. Intensity can be scaled by adjusting the number of repetitions and load, modifying the range of motion, or extending rest periods as needed. As participants adapt to the training, progression will be achieved by gradually increasing the complexity, intensity, or volume of the workouts [73]. The program will be led by an instructor with a degree in physical activity and sport sciences, who has experience in implementing physical exercise programs for young adults.

**Table 1 pone.0328538.t001:** High-intensity functional training (HIFT) protocol.

Week	Session	Type of session	Duration (min)	Sets	Exercises × Reps/ Time
**1**	1	EMOM	15	5	Push-ups × 15, Air squats × 20, Plank × 30 Seconds
	2	FT	15	4	Fons triceps × 20, Lunge × 40, Burpees × 20, Mountain climbers × 40
**2**	1	EMOM	15	5	Fons triceps × 15, Lunge × 24, Jumping jacks × 35
	2	AMRAP	15	∞	Thrusters × 20, Burpees × 20, Push-ups × 20
**3**	1	EMOM	20	5	Push-ups × 15, Air squats × 20, Burpees × 20, Sit-ups × 15
	2	FT	20	4	Fons triceps × 20, Lunge × 40, Burpees × 20, Mountain climbers × 40, Thrusters × 30
**4**	1	EMOM	20	5	Push-ups × 15, Hip thrust × 30, Jumping jacks × 35, Plank × 30 seconds
	2	AMRAP	20	∞	Shoulder press × 20, Burpees × 20, Push-ups × 20, Air squats × 40
**5**	1	EMOM	25	5	Fons triceps × 15, Hip thrust × 30, Burpees × 15, Plank × 40 seconds, Jumping jacks × 40
	2	AMRAP	25	∞	Shoulder press × 20, Burpees × 20, Sit-ups × 20, Air squats × 20
**6**	1	EMOM	25	5	Push-ups × 20, Lunge × 30, Skipping × 40, Hip thrust × 20, Mountain climbers × 30
	2	FT	25	4	Thrusters × 40, Push-ups × 40, Air squats × 40, Sit-ups × 40
**7**	1	EMOM	15	5	Pike push-ups × 15, Squat leg rises × 20, Spider plank × 40
	2	FT	15	4	Bent-over row × 20, Lateral lunge × 40, Skipping × 40, V-ups × 20
**8**	1	EMOM	15	5	Fons triceps × 15, Lateral lunge × 24, V-ups × 25
	2	AMRAP	15	∞	Bent-over row × 20, Sumo squat × 20, Pike push-ups × 20
**9**	1	EMOM	20	5	Pike push-ups × 15, Lateral lunge × 30, Spider plank × 40, Burpees × 10
	2	FT	20	4	Bent-over row × 20, Squat leg raises × 40, Jumping jacks × 35, V-ups × 20, Thrusters × 30
**10**	1	EMOM	20	5	Hand release push-ups × 15, Hip thrust × 30, Skipping × 40, Lateral lunge × 30
	2	AMRAP	20	∞	Alternating hand plank × 15, Sumo squat × 40, Pike push-ups × 20, V-ups × 30
**11**	1	EMOM	25	5	Pike push-ups × 20, Sumo squat × 20, Plank × 40 seconds, Burpees × 20, Skipping × 40
	2	AMRAP	25	∞	Bent-over row × 20, Squat leg raises × 20, Hand release push-ups × 20, Sit-ups × 20
**12**	1	EMOM	25	5	Pike push-ups × 20, Lateral lunge × 30, Alternating hand plank × 15, Jumping jacks × 40, Spider plank × 40
	2	FT	25	4	Hand release push-ups × 20, Sumo squat × 40, V-ups × 40, Thrusters × 40

EMOM, Every minute on the minute; FT, For time, AMRAP, As many rounds as possible;

∞, Infinite.

#### Mindfulness-based stress reduction intervention.

The program will comprise a 120-minute online synchronous session and two individual practice sessions per week, each lasting 20–40 minutes. Participants will receive a coursebook aligned with each class session, featuring: (1) a session introduction, (2) theoretical concepts, (3) key practical themes, (4) a weekly practice guide, (5) additional reading materials, and (6) visual resources. Audio recordings will also be provided in MP3 format. The applied method will follow the official MBSR program guidelines developed by Jon Kabat-Zinn [74], with some adaptations based on our previous work [75]. The program will be extended to 12 weeks to align with the HIFT and QG programs. Key changes include: (1) Session 0: A 2-hour introductory session featuring an overview, distribution of materials, and the basics of mindfulness practice, (2) An all-day practice session of approximately 6 hours, scheduled between Sessions 6 and 7, (3) Two unscheduled weeks (between Sessions 3 and 4, and between the practice day and Session 7), during which participants will be encouraged to maintain autonomous practice using the provided materials and recordings. The program will be led by a certified mindfulness instructor affiliated with the MBSR Professional Association of Mindfulness Instructors.

#### Qigong intervention.

Like HIFT, the QG intervention will consist of two 60-minute weekly online synchronous group sessions and one individual autonomous session, giving participants the opportunity to revisit any session of their choice from that week. In addition to Zoom, Open Broadcaster Software (OBS) will combine music, PowerPoint slides, and live broadcasts. Participants will be asked to find a peaceful space with fresh air, ideally measuring 3m x 2m and free of objects. The sessions will consist of three parts: (1) Warm-Up: The “Three Gates” exercise and the “Five Harmonies” of Liu Ya Fei, focusing on spine and joint strengthening; (2) Main Part: The 8 Qigong exercises from the Standardized Baduanjin Qigong for Health, as instructed by the Chinese Health Qigong Association [76]. This includes reviewing previous exercises, joint practice, and supervised practice; (3) Self-Massage: A selection of self-applied Tui-na massages. The training program will be led by two qualified and certified instructors from the Qigong Institute of Barcelona. One will primarily demonstrate the exercises, while the other provides explanations and monitors participants’ performance. The dual-instructor format is considered beneficial for ensuring safety and clarity in instruction, which emphasizes precise postural alignment and breathing. Efforts will ensure consistency in instructional content and participant interaction across all interventions.

#### Virtual reality-based physical exercise and mind-body interventions.

The immersive VR system will be co-designed through a structured focus group involving six participants, consisting of university students and professionals. The focus group aims to explore the integration of well-being interventions into VR environments. One session will be conducted online via Zoom and will last approximately 60 minutes. A moderator will guide the discussions using a structured interview script (S4 File). The discussions will revolve around key questions concerning the feasibility, advantages, and challenges of implementing these practices in a VR environment. The sessions will be recorded using Zoom’s built-in recording feature, with participants’ prior consent. The recordings will then be transcribed and analyzed thematically. All responses will remain anonymous, and data will be securely stored on the university’s server. Session characteristics (e.g., frequency, duration) will be informed initially by existing literature on VR-based well-being interventions and further adapted throughout the co-design process to determine the optimal configuration for delivering VR-based interventions. Expert evaluations and usability assessments will ensure that the intervention meets user needs and well-being objectives. A computer science technician will develop the VR environments using Unity, a widely used real-time 3D development engine [77]. These environments will feature realistic avatars representing the participants. The proficient instructors who conducted the training in Study 1 will also be involved in developing the VR programs for Study 2. Participants will be provided with Meta Quest 3S headsets (Meta) to train remotely, fully utilizing the potential of VR through embodiment, body tracking, music, and immersive environments such as natural settings.

### Intervention adherence

In Study 1, attendance for online classes will be recorded and tracked by instructors using Excel spreadsheets. Participants will self-report their independent practice sessions using a questionnaire administered via Microsoft Forms. This will capture the frequency and duration of autonomous practice. Furthermore, participants will have the option to provide comments on their experiences. A researcher will review these records weekly, verify the accuracy of the data, and update instructors on participants’ training status. Adherence will be assessed based on session attendance and the total time spent on both supervised and independent practice. Participants in Study 2 will also record their attendance in a Microsoft Forms questionnaire, which will subsequently be reviewed by a researcher. Adherence will be based on session attendance and VR training duration.

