**Fig 2 pone.0328538.g002:**
[figure not shown]
Key variables of interest in the YoungFitT study. HIFT: High-Intensity Functional Training, MBSR: Mindfulness-Based Stress Reduction Therapy, QG: Qigong, VR: Virtual Reality, HRV: Heart Rate Variability.

The key hypotheses for this objective are: (1) All three interventions will positively affect psychological well-being and cognitive functions at 12 weeks compared to baseline, with each intervention showing a specific profile of outcomes (HIFT: more cognitive gains; MBSR: more psychological gains; QG: moderate benefits in both areas). These positive effects are expected to persist at the 12-week follow-up; (2) All interventions are expected to induce changes in physical components (increased physical activity and fitness status), mental components (enhanced mindful thinking and sleep quality), physiological stress markers (increased HRV), and microbial composition (increased diversity), which will mediate improvements in psychological well-being and cognitive outcomes; (3) Sociodemographic factors (sex and age) and individual factors (cognitive reserve and general intelligence) will moderate changes in outcomes from pre- to post-intervention.

**Study 2 focuses on VR-based physical exercise and mind-body interventions.** The primary objective of this proof-of-concept study is to test the feasibility and preliminary effectiveness of VR-based HIFT, MBSR, and QG interventions on the psychological well-being and cognitive functions of university students. The specific objectives of this study include: (1) Generating virtual environments for HIFT, MBSR, and QG interventions; (2) Evaluating the usability, acceptability, and feasibility of these VR interventions; (3) Studying the effectiveness of VR interventions as depicted in Fig 2; and (4) Exploring the effects and adherence of these VR-based physical exercise and mind-body interventions compared to non-VR interventions.

It is hypothesized that: (1) All VR interventions will positively affect psychological well-being and cognitive functions after 12 weeks, with each intervention displaying distinct outcomes (HIFT: cognitive gains; MBSR: psychological gains; QG: moderate benefits); and (2) VR-based interventions will yield better adherence and greater benefits compared to non-VR interventions.

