#### Usability and feasibility of VR interventions.

The quantitative assessment of the VR system’s usability will be conducted using the System Usability Scale (SUS), with scores ranging from 0 to 100, where higher scores indicate greater usability [102]. The feasibility of the VR program will be assessed through the following: (1) Measuring engagement levels, based on adherence rates, including session attendance and time spent in VR; (2) Evaluating program acceptability by collecting participant feedback through structured interviews, guided by the Unified Theory of Acceptance and Use of Technology (UTAUT), to better understand their experience with the VR intervention; (3) Analyzing effectiveness, using outcome measures relevant to the study objectives.

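### Class attendance is instructor-logged in Study 1 but attendance is self-recorded in Study 2, which leaves the planned VR versus non-VR adherence comparison open to differential measurement error

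*Protocol article*

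**What the plan says.** The section 'Intervention adherence' fixes the recorder for each study. For Study 1: "In Study 1, attendance for online classes will be recorded and tracked by instructors using Excel spreadsheets". Practice outside class is handled differently: "Participants will self-report their independent practice sessions using a questionnaire administered via Microsoft Forms". Both sets of records are then checked: "A researcher will review these records weekly, verify the accuracy of the data, and update instructors on participants’ training status". The Study 1 measure combines the two sources: "Adherence will be assessed based on session attendance and the total time spent on both supervised and independent practice".

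For Study 2: "Participants in Study 2 will also record their attendance in a Microsoft Forms questionnaire", and a researcher reviews the form later. Adherence there rests on attendance and the duration of VR training. The source of the duration is not stated.

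Under 'Objectives and hypotheses', objective 4 of Study 2 is to explore effects and adherence against the non-VR programmes, and the second hypothesis is directional: "VR-based interventions will yield better adherence and greater benefits compared to non-VR interventions". The section on usability and feasibility of the VR interventions also makes engagement a feasibility criterion, "based on adherence rates, including session attendance and time spent in VR".

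**The concern.** A between-study comparison of adherence needs a measure that behaves in the same way in both studies. Here part of the Study 1 measure is an observer's record, while the whole of Study 2 attendance is the participant's own entry. Because the recording method coincides with the exposure, no later adjustment can separate the two.

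The checking also differs as written. In Study 1 a researcher verifies accuracy every week. In Study 2 a researcher reviews the form afterwards, and no independent record is named to check it against.

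Better adherence is a leading reason that the article gives for using VR. A gap produced by the recording method could be read as support for the hypothesis, or could hide a true advantage, and would then be carried into the larger studies that Study 2 is meant to inform.

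**Working it through.** **Plan's own figure.** The article gives no power, effect size or SD for adherence. Its only sample-size figure is for the Study 1 omnibus ANOVA, and it reproduces: N = 159 gives a critical F of 3.054 and power 0.805, and 159/(1 − 0.10) = 176.7, hence 177. It has no bearing on adherence beyond supplying the number of participants.

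**Step 1: how much of Study 1 is observer-recorded.** From the intervention sections, per week:
- HIFT: two group sessions and one autonomous session, so 2/3 instructor-logged.
- QG: two group sessions and one autonomous session, so 2/3.
- MBSR: one group session and two individual sessions, so 1/3.
- Average with equal arms: (2/3 + 2/3 + 1/3)/3 = 5/9.

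By session count the recording contrast is therefore weakest for MBSR. By planned time this ordering need not hold. The MBSR class lasts 120 minutes against 40 to 80 minutes of individual practice, so 120/200 to 120/160, or 60% to 75%, is class time. HIFT and QG have 120/180 = 67% if the autonomous session also lasts 60 minutes.

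**Step 2: size of a spurious gap.** Assume equal true attendance p in both studies, a share o of missed sessions reported as attended wherever self-report is used, every Study 2 session self-reported, and three planned sessions a week in both studies. Apparent VR advantage = (1 − p) × o × s, where s is the instructor-logged share of the Study 1 sessions counted. None of p or o is in the documents. For p from 0.6 to 0.8 and o from 0.1 to 0.3:

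| Study 1 sessions counted | s | Smallest | Largest |
|---|---|---|---|
| Classes only | 1 | 0.2 × 0.1 = 2 points | 0.4 × 0.3 = 12 points |
| All, HIFT or QG | 2/3 | 1.3 points | 8 points |
| All, MBSR | 1/3 | 0.7 points | 4 points |

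With o = 0, or the same recording method in both studies, the gap is zero. If forms go unsubmitted, the sign reverses.

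**Step 3: how often such a gap would pass a test.** Assume a two-sided 5% comparison of mean attendance with a common SD. For SD 25, SE = 25 × √(1/45 + 1/177) = 4.17 points. With inflation b of self-reported attendance, P(false 'VR better') = Φ(k·b/SE − 1.96), where k = 1 for classes only and k = 5/9 if all weekly sessions count and both forms are inflated equally.

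| Inflation b | Classes only (k = 1) | All sessions (k = 5/9) |
|---|---|---|
| 5 points | 22% | 10% |
| 10 points | 67% | 26% |
| 15 points | 95% | 51% |

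At 10 points, SD 20 to 30 gives 85% to 51% for classes only and 38% to 20% for all sessions. The nominal rate in this direction is 2.5%. An inflation of 15 points exceeds anything that the assumptions in Step 2 produce, so the last row is an extreme case.

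**The case against.** The strongest reply is that the contrast is not observed against self-reported. Study 1 adherence already mixes instructor logs with the same kind of form that Study 2 uses, so part of any over-reporting cancels. This stands, and it is why the all-sessions column is given.

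Second, a reader might infer that adherence in Study 1 is instructor-logged throughout and that the VR comparison is therefore biased towards VR. The documents do not support that. They give no over-reporting rate, forgotten forms would push the other way, and a researcher reviews the records in both studies.

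Third, the article specifies no significance test of adherence between the studies. Objective 4 is exploratory, and the Discussion calls the Study 2 findings preliminary. The rejection rates therefore illustrate scale and do not describe a planned decision.

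Fourth, VR duration may already come from the headset, and an article may leave that to the full protocol. That is possible for duration. It does not extend to attendance, whose source the article states explicitly. Session format is also still to be settled by co-design. If VR training turns out to be unsupervised, self-reported independent practice in Study 1 is a natural like-for-like comparator, and those data are already planned.

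Finally, the comparison is non-randomised, across different recruitment waves and possibly different session schedules. Harmonised recording would not make it causal. That limits what the fix achieves, but it does not justify leaving in a further distortion that can be avoided.

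**Conclusion.** The concern holds in a limited form. The stated recording methods differ between the studies for class attendance against VR attendance, and a directional adherence hypothesis rests on comparing the two. The comparison is open to differential error of unknown size, favouring VR under over-reporting and disfavouring it under non-submission. By session count the effect is largest when Study 1 classes are set against VR sessions and smallest for MBSR when all sessions count. Under the illustrative assumptions the spurious gap runs from about 1 to 12 points. That is enough to matter at 45 versus 177 participants, but the SD, the inflation and the test are all assumptions. The change is worth making because adherence is a stated objective and a feasibility criterion, and the repair lies within the project's control.

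**What to change.** In 'Intervention adherence', state that Study 2 attendance and VR training duration come from time-stamped session starts and ends logged by the Unity application. Keep the questionnaire as back-up and as the self-report measure.

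Define adherence in both studies as a percentage of planned sessions, once co-design has fixed the planned number for VR. Limit the exploratory comparison between the studies to components recorded alike: logged VR sessions against instructor-logged classes, and self-report against self-report. Report the results as non-randomised and preliminary.

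The cost is modest programming and a short addition to the text. The project develops the application and supplies the headsets, and the article places the first Study 2 wave in September 2025, so logging is best added before release. Some log data will be lost to device faults, and the questionnaire can then fill gaps if those sessions are flagged. Scheduled group classes and remote VR sessions will still differ in format, which the report should say.
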